### Study population

In total 600 consenting participants will be recruited. Patients are considered eligible if they are diagnosed with T2DM and meet the following criteria:

❑ known disease duration of over 1 year

❑ recent HbA1c ≥ 7.0%

❑ treated with diet and/or oral hypoglycaemic agents

❑ do not require insulin at inclusion

❑ aged between 45 and 75 years

❑ used SMBG or SMUG less than 3 times in the previous year

Participants will be randomly assigned to one of the following 3 groups (figure 1):

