### Intervention groups (SMBG & SMUG)

Following randomization participants allocated to one of the intervention groups receive a training in SMBG or SMUG delivered by trained research assistants and a flowchart with instructions when to perform and how to interpret self-monitoring. After this training participants should be able to perform SMBG or SMUG and interpret the results, identify factors that can influence glucose level and identify when additional tests are needed.

The acquired skills in self-monitoring are checked and if necessary corrected in a control visit of maximal 30 minutes, 7 to 14 days after randomization. During this visit a stepwise script outlining the self-monitoring skills needed is used. All participants in the SMBG group are requested to measure their blood glucose twice a week (one weekday, one weekend day) at 6 different time points a day (fasting, 1 1/2 – 2 hrs after breakfast, before lunch, 1 1/2 – 2 hrs after lunch, before diner, before bedtime) with a glucose-meter (LifeScan OneTouch^® ^Ultra^®^2). Participants in the SMUG group are requested to test their urine twice a week (one weekday, one weekend day) in the evening after dinner (Urispec™ plus urine glucose in vitro reagent test strips). Both groups will receive a diary in which they have to record the obtained values for blood or urine glucose. To avoid extra psychological burden we allow participants to adjust self-monitoring to a frequency 'they feel comfortable with' starting from 2 months after baseline until the end of the study.

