### Process evaluation and quality assurance

A process evaluation will be performed to evaluate our theories of the processes underlying the effect of self-monitoring. For this evaluation changes in mastery are assessed by the subscales personal control and treatment control of the Revised Illness Perception Questionnaire (IPQ-R) [33] and changes in perceptions of diabetes and social support by the subscales perceived severity and perceived social support from a significant other of the Multidimensional Diabetes Questionnaire (MDQ) [34]. These measures are assessed at 5 time-points (baseline, 2 months, 4 months, 6 months and 12 months) (Table 1).

A script outlining the topics to be covered per visit is used to support the nurses and research assistants in their tasks. Before inclusion all research assistants attend a training in self-monitoring (SMBG and SMUG) and before the start of the intervention their self-monitoring skills are tested in a pilot. During the inclusion period the research assistants are audited. Directly after the training the research assistants are asked about their opinions about their acquired skills in self-monitoring and their capability to train and instruct participants following protocol (5-point Likert scale; 1 = fully disagree, 5 = fully agree). This will also be done after the inclusion period. The participants of the intervention groups are asked to give their opinion on 6 items regarding skills, importance and motivation for self-monitoring at baseline and 2 months after baseline (5-point Likert scale).

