### Analyses

On the basis of an intention-to-treat analysis, differences between the intervention groups and usual care group are calculated with 95% confidence intervals. In addition per protocol analyses will be performed. The subgroups SU and non-SU will be analysed separately for all outcome measures. In case there is no effect modification by treatment the data of both subgroups will be pooled. If there are any relevant differences in baseline measurements between the 3 arms, we will adjust the outcomes for these factors (i.e. age, gender, ethnicity, status of depression, diabetes duration, marital status, level of education). Linear and logistic regression will be used to determine the effect of the intervention on each of the outcome measurements. The effect of the intervention will be estimated for sub-groups defined by duration of diabetes, socio-economic status, perceived social support and perceived severity of diabetes, glycaemic control and self-monitoring frequency in order to gain a better understanding as to who benefits most from the intervention. Analyses of moderators and mediators will be performed for the process-evaluation.

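### Self-monitoring frequency is listed as a subgroup for the intervention effect, but it is chosen after randomisation and has no assigned or diary-recorded counterpart in usual care, so those estimates are not randomised comparisons

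*Protocol article*

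**What the plan says.** The Analyses section defines the trial's effects as comparisons with usual care: "differences between the intervention groups and usual care group are calculated with 95% confidence intervals". It then turns to subgroups: "The effect of the intervention will be estimated for sub-groups defined by duration of diabetes", followed by socio-economic status, perceived social support and, last, "perceived severity of diabetes, glycaemic control and self-monitoring frequency in order to gain a better understanding as to who benefits most from the intervention". Moderator and mediator analyses for the process evaluation are announced in a separate sentence.

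Three other places decide what frequency can mean here:

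- **Study population.** To be eligible, a patient must have "used SMBG or SMUG less than 3 times in the previous year".
- **Intervention groups (SMBG & SMUG).** A schedule is requested at the start. After that, "we allow participants to adjust self-monitoring to a frequency 'they feel comfortable with' starting from 2 months after baseline", until the study ends. Glucose diaries are described for the two intervention groups only.
- **Discussion.** The article cites a report that testing more than once a day went with diabetes-related distress in patients not on insulin. It presents the freedom to adjust frequency as a safeguard against such distress.

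**The concern.** A subgroup effect from a randomised trial can be read causally when the subgroup is fixed before randomisation and can be identified in every arm. Self-monitoring frequency meets neither condition. It takes shape after randomisation, it is partly the participant's own choice, and the article gives no way to place usual-care patients in a high- or low-frequency group.

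The choice is also tied to a primary outcome. Participants adjust frequency to what is comfortable, and the article's stated reason for allowing this is to limit distress. PAID measures that distress. Grouping by frequency may therefore group participants partly by outcome.

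At stake is the answer to the article's own question of who benefits. Frequent and infrequent monitors could appear to benefit differently when the intervention does nothing for either.

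**Working it through.** **1. Can the variable be read as a baseline characteristic?** No. Every participant has 0, 1 or 2 self-tests in the previous year, which leaves almost no variation. The subgroup can only be frequency during the trial.

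**2. Is there a matching group in usual care?** The article assigns no self-monitoring there and describes no glucose diary for that arm. The available comparator for any frequency subgroup is the whole usual-care group.

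**3. Inputs, and a check of them.** From the Sample size section: PAID SD 20, minimal important difference 10 (0.5 SD), α 0.025, power 0.85. The article's own figure reproduces:

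n per group = 2 × (2.241 + 1.036)² / 0.5² ≈ 86 (two-sided, normal approximation)

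The abstract gives 200 per group. With 15% drop-out, 200 × 0.85 = 170 remain.

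**4. Size of the bias when the true effect is zero.** Let chosen frequency have correlation r with the PAID outcome. The documents do not give r, so it is an assumption, taken as 0, 0.1 and 0.3 with either sign. For jointly normal variables and a median split, each half's mean is displaced from the arm mean, and hence from usual care, by

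|r| × √(2/π) × SD = |r| × 0.798 × 20

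| Assumed \|r\| | Each half versus usual care (PAID points) | In SD units |
|---|---|---|
| 0 | 0 | 0 |
| 0.1 | 0.1 × 0.798 × 20 = 1.6 | 0.08 |
| 0.3 | 0.3 × 0.798 × 20 = 4.8 | 0.24 |

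The two halves move in opposite directions. If r is negative, frequent monitors look less distressed than usual care. If r is positive, they look more distressed.

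**5. Simulation check.** With 170 per arm, no true effect and 4,000 runs per value of r, the mean displacements were about 1.6 points at |r| = 0.1 and 4.7 to 4.8 at |r| = 0.3, agreeing with the formula. A nominal 5% test of the high-frequency half against usual care rejected in about 5% of runs at r = 0, 9 to 10% at |r| = 0.1 and about 45% at |r| = 0.3.

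**6. Pooling the two intervention arms.** The requested starting schedules are 2 days × 6 tests = 12 a week for SMBG and 2 days × 1 test = 2 a week for SMUG. A common cut-off would largely separate the two monitoring methods rather than types of patient.

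**The case against.** The best defence is that this is one item in an explanatory list, meant to aid understanding, and that a condensed article need not spell out the method. The analysis is indeed exploratory, and that limits the consequences. But the article states the analysis and its purpose. It places frequency beside legitimate baseline subgroups and attaches no warning that the comparison is non-randomised. The problem is what is stated, not detail left to an analysis plan.

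Several stronger readings are tempting, and the documents do not support them:

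- **Frequent monitors will look better.** The direction cannot be derived. Distressed participants may cut back, but the association cited in the Discussion runs the other way, with more testing going with more distress.
- **The bias nearly equals the minimal important difference.** The gap between the two halves is twice the figures above (about 3.2 and 9.6 points). The 10-point difference, however, was set for a comparison between groups, so the like-for-like figure is one half against usual care: 1.6 or 4.8 points, under half of 10.
- **Perceived severity, social support and glycaemic control are faulty subgroups too.** They are measured repeatedly, but also at baseline, and the article nowhere says that later values will define the subgroups.
- **The per protocol analysis has the same flaw.** The article gives no definition of that set, so nothing stated can be criticised.
- **Self-monitoring does not exist in usual care.** The article does not forbid it. It is only unassigned and not covered by the glucose diary.

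**Conclusion.** The point stands for self-monitoring frequency alone. As written, the analysis contrasts self-selected monitors with unselected controls, and it is unbiased only if chosen frequency is unrelated to prognosis. The article's own rationale for flexible frequency makes that hard to assume.

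Under the assumptions in the table, the spurious difference of each half from usual care is 0 to 4.8 PAID points, of unknown sign. These figures rest on an assumed correlation, normality, a median split and the quoted SD of 20. If the analysed outcome is a change score with another SD, they scale in proportion.

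A reader might infer that the main result is compromised. It is not: the intention-to-treat comparison, the significance level and the sample size do not depend on this item.

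**What to change.** In the Analyses section, delete self-monitoring frequency from the subgroups in which the intervention effect is estimated. Move it to the process evaluation, for example:

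> The relation between self-monitoring frequency and outcome will be described within the SMBG arm and within the SMUG arm separately. This is a non-randomised exposure-response description and will not be interpreted as an effect of the intervention in subgroups.

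The arms are kept apart because their requested schedules differ.

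A complier-type estimate using randomisation as the instrument is not an easy substitute. It requires assignment to act only through monitoring, whereas the intervention arms also receive training, a control visit and an interpretation flowchart, any of which could affect confidence or distress directly.

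The change is to wording only, with no extra patients, visits or significance level. The cost is that one exploratory table loses its causal interpretation.

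### Effects estimated within subgroups do not by themselves show who benefits most; estimate arm-by-baseline-moderator interactions, and keep self-monitoring frequency out of that analysis

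*Protocol article*

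**What the plan says.** The Analyses section of the protocol article states the step as follows: "The effect of the intervention will be estimated for sub-groups defined by duration of diabetes, socio-economic status, perceived social support and perceived severity of diabetes". Two further factors, self-monitoring frequency and glycaemic control, bring the list to six, and the purpose is given as "in order to gain a better understanding as to who benefits most from the intervention".

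Three neighbouring statements bear on how this should be read.

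- The next sentence adds: "Analyses of moderators and mediators will be performed for the process-evaluation". It does not describe the method.
- For the stratification factor (sulfonylurea or glinide use, SU), each stratum is to be analysed on its own, and the section adds a condition: "In case there is no effect modification by treatment the data of both subgroups will be pooled". This condition on effect modification is attached to SU status only.
- The section on process evaluation describes that evaluation as covering, besides personal and treatment control, "changes in perceptions of diabetes and social support by the subscales perceived severity and perceived social support". Diabetes duration, socio-economic status and glycaemic control are not among the measures it lists.

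**The concern.** Asking who benefits most means asking whether the effect in one kind of patient differs from the effect in another. That quantity is the difference between two subgroup effects, with its own standard error. The sentence that states the aim names only the effect within each subgroup. If such estimates are set side by side, one confidence interval may exclude zero and the other may not, although the true effects are equal. A reader may then take the first group as the one that benefits. At stake is advice on which non-insulin-treated patients should be offered self-monitoring.

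The factors also differ in kind. Five of them can be fixed at baseline. The sixth, self-monitoring frequency, cannot: the section on the intervention groups lets participants adjust it from 2 months after baseline, and the usual-care arm is assigned no self-monitoring.

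**Working it through.** **Inputs.** From Sample size: a relevant difference of 0.5 SD (10 PAID points, SD 20), α 0.025, β 0.15, 86 per group, doubling for the SU strata, 15% drop-out, 600 in total. From the Abstract: 200 per arm. Assumptions of this check: each factor splits patients 50/50, one arm comparison, one outcome, normal approximation, two-sided tests.

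**1. The plan's own figure.** n = 2(z₀.₉₈₇₅ + z₀.₈₅)²/0.5² = 2(2.241 + 1.036)²/0.25 ≈ 86 per group, as stated. Then 86 × 2 strata × 3 arms = 516, and 516/0.85 ≈ 608 (or 516 × 1.15 ≈ 594), close to 600. No sample-size figure is in question here.

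**2. Size of a half-subgroup.** 200 × 0.85 = 170 completers per arm, and 170/2 = 85 per arm per half.

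**3. Chance that exactly one half is significant when the true effect is identical.** The standard error of the effect in one half is √(2/85) = 0.153 SD. With power p in each half, the chance is 2p(1 − p). At 0.05:

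| True effect in both halves | p | Exactly one half significant |
|---|---|---|
| 0 | 0.050 | 9.5% |
| 0.25 SD (5 PAID points) | 0.371 | 46.7% |
| 0.3 SD (6 points) | 0.498 | 50.0% |
| 0.5 SD (10 points) | 0.903 | 17.5% |

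A two-sample t calculation gives 18.0% in the last row. At 0.025 the four figures are about 5%, 40%, 48% and 26%.

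Over five baseline factors, the expected number of such false contrasts is 5 × 0.175 ≈ 0.9 at 0.5 SD and 5 × 0.467 ≈ 2.3 at 0.25 SD, for one comparison and one outcome.

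**4. What an interaction estimate offers.** Its standard error is √(4/85) = 0.217 SD, and a test at 0.05 has a 5% false-positive rate per factor whatever the common effect.

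- Power for a 0.5 SD difference between subgroup effects: Φ(0.5/0.217 − 1.96) ≈ 63% (53% at 0.025).
- Power for a 0.25 SD difference: about 21%.
- Difference detectable with 80% power at 0.05: (1.96 + 0.842) × 0.217 ≈ 0.61 SD, about 12 PAID points.
- Number per cell for 85% power at 0.5 SD: 4 × ((1.96 + 1.036)/0.5)² ≈ 144, against 85 available.

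**5. Multiplicity that remains.** With five independent factors, the chance of at least one false-positive interaction is 1 − 0.95⁵ ≈ 23%. With 5 factors × 2 comparisons with usual care × 2 primary outcomes = 20 tests, 20 × 0.05 = 1 is expected by chance.

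**6. Self-monitoring frequency.** Eligibility requires fewer than 3 uses in the previous year, so its baseline value hardly varies. Its later value is chosen after randomisation and does not exist as a planned quantity in usual care. No arm-by-frequency term would therefore be a randomised contrast.

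**The case against.** The strongest reply is that the article does not ignore effect modification. It announces moderator analyses directly after the subgroup sentence, makes the pooling of SU strata depend on effect modification, and in the Discussion expects to detect an interaction with treatment type. Regression is the stated model, and in regression a moderator analysis is ordinarily an arm-by-moderator term. The subgroup sentence does not say that the six groups will be analysed separately; that word is used only for SU status. Estimating effects for subgroups is compatible with taking them from an interaction model. A condensed article may leave the exact term to a fuller document.

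Much of this stands. It rules out three stronger readings that a reader might infer:

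- **That the plan has no interaction analysis, or will compare subgroups by significance.** The text says neither. The figures in step 3 show what such a reading of results would cost; they do not describe an announced rule.
- **That subgroups will be formed on HbA1c, perceived severity or social support measured after randomisation.** All three are measured at baseline (Table 1), and nothing says that later values will be used. Naming baseline is a safeguard against a risk, not the correction of a stated error.
- **That false contrasts arise in 47% of trials even at the design effect of 0.5 SD.** That needs a further split inside one SU stratum (about 42 per arm per half, power 62%) and equal strata. In the pooled sample the figure is about 18%.

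The reply does not remove the mismatch in the sentence itself. The moderator analyses are tied to the process evaluation. They plausibly reach perceived severity and social support, but not clearly the other three baseline factors. The SU condition does not extend to any of the six.

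**Conclusion.** The point holds as a mismatch between a comparative aim and a stated step that only estimates effects within subgroups. It concerns secondary, exploratory analyses and leaves the primary comparisons and the sample size untouched. If within-subgroup results were read side by side, equal effects would look different in about 18% of trials per factor at 0.5 SD and about 47–50% at 0.25–0.3 SD. This assumes 50/50 splits, 85 completers per arm per half and a 0.05 threshold. The document gives no subgroup proportions, so these figures illustrate the scale. Interaction estimates address the question asked, but with modest power and without removing multiplicity.

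**What to change.** Replace the subgroup sentence with wording to this effect:

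- For diabetes duration, socio-economic status, perceived social support, perceived severity and HbA1c, use the value at baseline, and keep it continuous where it was measured so.
- For each factor, estimate the arm-by-moderator interaction with its confidence interval in the intention-to-treat sample.
- Derive any subgroup effects from that model, and label all of these results exploratory.
- Leave self-monitoring frequency out of this analysis. Report it only as a descriptive, non-randomised association within the two intervention arms.

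If a statistical analysis plan already says this, a reference to it is enough. The cost is analysis wording only, with no change to conduct or sample size. The downside is that interaction estimates are less precise than subgroup estimates (standard error 0.217 against 0.153 SD), so fewer subgroup claims will be possible.

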### Economic analyses

For the economic evaluation from both the societal and the health insurer perspective all costs related to diabetes, and diabetic complications are considered relevant. Costs of the intervention (SMBG or SMUG, visits to the GP, medical specialists, therapists, dieticians and hospitalization) are considered direct healthcare costs. The costs of i.e. absence from paid and unpaid work are considered indirect healthcare costs. Differences in mean costs between the groups will be presented with 95% confidence intervals. An incremental cost-effectiveness ratio (ICER) will be given both for PAID and CIDS by dividing the incremental mean costs by the incremental mean reduction in PAID or CIDS score. A cost utility ratio will estimate the incremental costs per Quality Adjusted Life Year gained for the study period. Cost-effectiveness planes and acceptability curves will be presented and 95% confidence intervals will be estimated for the ICERs.

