## Abstract

**Background:**

Diabetes specific emotional problems interfere with the demanding daily management of living with type 2 diabetes mellitus (T2DM). Possibly, offering direct feedback on diabetes management may diminish the presence of diabetes specific emotional problems and might enhance the patients' belief they are able to manage their illness. It is hypothesized that self-monitoring of glucose in combination with an algorithm how and when to act will motivate T2DM patients to become more active participants in their own care leading to a decrease in diabetes related distress and an increased self-efficacy.

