**Discussion:**

The IN CONTROL-trial is designed to explore whether feedback from self-monitoring of glucose in T2DM patients who do not require insulin can affect diabetes specific emotional distress and increase self-efficacy. Based on the self-regulation model it is hypothesized that glucose self-monitoring feedback changes illness perceptions, guiding the patient to reduce emotional responses to experienced threats, and influences the patients ability to perform and maintain self-management skills.

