### Measurements

Outcome measures are obtained at baseline, 4 and 12 months. These are collected by self-administered questionnaires, blood sampling and anthropometry. Diabetes specific distress is assessed by the Problem Areas In Diabetes scale (PAID) [24,25] and self-efficacy by the Confidence In Diabetes Self-care questionnaire (CIDS) [26] adjusted for T2DM. Patient treatment satisfaction is assessed by the Diabetes Treatment Satisfaction Questionnaire (DTSQ) [27], physical activity is assessed by the short International Physical Activity Questionnaire (IPAQ-7) [28], health status and cost utility are assessed with the Euroqol-5D [29-31]. Status of depression is assessed at baseline and at 12 months using the Patient Health Questionnaire-9 (PHQ-9) [32], Demographic variables on age, gender, diabetes duration, marital status and level of education are assessed at baseline by means of a self-administered questionnaire. Glycaemic control is measured by HbA1c-level. Furthermore, BMI and blood-pressure are measured. Participants are asked to register occurrence of hypoglycaemia in care-diaries. Costs of direct health care and indirect non-healthcare will be inventoried in cost-diaries and recorded in 3-monthly intervals. Table 1 summarizes the measures and their timing.

**Table 1 T1:** Study measures

**Measures**	**Baseline**	**2 months**	**3 months**	**4 months**	**6 months**	**9 months**	**12 months**

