### Sample size

The proposed trial is designed to detect a clinically relevant change of self-monitoring of glucose on diabetes specific emotional distress and self-efficacy. No consensus exists about minimal important differences (MID) of diabetes specific distress measured with the PAID and self-efficacy measured with the CIDS. Therefore we set the MID at half a standard deviation [35]. In diabetes patients the standard deviation (SD) of PAID (scores transformed to 0–100) was 20 points [25]. Using a bonferroni correction based on two primary hypotheses with α 0.025 and β 0.15, a sample size of 86 per group is needed to find a difference of 10 points (0.5 SD). Information on the SD of the CIDS is not yet available for T2DM patients. For type 1 diabetes patients the SD of CIDS (scores transformed to 0–100) was 12 points [26]. To detect a decrease of 6 points (0.5 SD), while correcting according to bonferroni based on two primary hypotheses with α 0.025 and β 0.15 a sample size of 86 per group is needed. Taking into account different effects in different treatment groups (SU or non-SU) pre-stratification by treatment will double the sample size. Assuming a 15% drop-out rate, a total of 600 T2DM patients with HbA1c ≥ 7.0% are needed in the study. In addition, with a total of 600 patients it is expected to have sufficient power to detect a clinically relevant decrease of 0.5% in HbA1c.

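### The cost-effectiveness ratio for self-efficacy is defined per point of CIDS reduction, which reverses its sign against the trial's own hypothesis

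*Protocol article*

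**What the plan says.** The Abstract (Background) gives the two primary outcomes opposite directions of benefit: self-monitoring is expected to work by "leading to a decrease in diabetes related distress and an increased self-efficacy". The Abstract (Discussion) repeats that feedback "can affect diabetes specific emotional distress and increase self-efficacy", and Previous research speaks of self-efficacy in the same direction.

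Measurements assigns distress to the PAID and "self-efficacy by the Confidence In Diabetes Self-care questionnaire (CIDS) [26] adjusted for T2DM".

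Two later sections treat both scales as if they should fall:

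- Economic analyses defines one ICER rule for both scales, "by dividing the incremental mean costs by the incremental mean reduction in PAID or CIDS score". It then promises cost-effectiveness planes, acceptability curves and 95% confidence intervals for the ICERs.
- Sample size plans the CIDS comparison "To detect a decrease of 6 points (0.5 SD), while correcting according to bonferroni based on two primary hypotheses". The parallel PAID sentence uses a neutral word, a difference of 10 points.

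The article nowhere says which end of the CIDS is favourable, and nowhere says that the scale is reverse-scored.

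**The concern.** An ICER is interpretable only if its denominator is an amount of benefit. For the PAID, a reduction is benefit. For a confidence scale, a reduction is loss. One shared denominator cannot serve two scales that point in opposite directions.

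At stake is the economic result for self-efficacy. An analyst who codes the rule literally would report a gain in confidence as a negative effect, and a loss of confidence as benefit bought at a price. The sign of an ICER is already hard to read, because a negative ratio arises both when an intervention is cheaper and better and when it is dearer and worse. The direction of the effect therefore has to be fixed correctly in the plan.

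**Working it through.** **1. Reproduce the plan's sample size and see whether direction matters.**

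Inputs from Sample size: "the SD of CIDS (scores transformed to 0–100) was 12 points", with a target of 6 points; "the standard deviation (SD) of PAID (scores transformed to 0–100) was 20 points", with a target of 10 points; α = 0.025; β = 0.15. The article does not state whether the test is one- or two-sided.

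Formula: n per group = 2 (z₁₋α/₂ + z₁₋β)² / (δ/SD)².

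- Standardised difference: 6/12 = 10/20 = 0.5.
- z values: 2.241 + 1.036 = 3.278, squared 10.744.
- n = 2 × 10.744 / 0.25 = 85.95, rounded up to **86**, as stated, for both scales.
- A one-sided test would give 72, so the stated figure implies a two-sided test.
- δ enters squared. With δ = −6 the result is again 86, with power 0.850 in either direction. The word *decrease* therefore has no numerical effect on the sample size.

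**2. Sign of the CIDS ICER.**

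Let ΔC be the incremental mean cost and ΔE the incremental mean change in CIDS, positive when confidence rises.

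- As written: ICER = ΔC / (−ΔE).
- Per point gained: ICER = ΔC / ΔE.
- Ratio of the two: −1, whatever the values of ΔC and ΔE.

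The article gives no cost figures. The table uses an assumed ±100 cost units purely as illustration, with the plan's own 6 points as the effect.

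| ΔC | ΔE (CIDS) | As written | Per point gained | True position | Position if effect is plotted as reduction |
|---|---|---|---|---|---|
| +100 | +6 | −16.7 | +16.7 | dearer, better | dearer, worse |
| +100 | −6 | +16.7 | −16.7 | dearer, worse | dearer, better |
| −100 | +6 | +16.7 | −16.7 | cheaper, better | cheaper, worse |
| −100 | −6 | −16.7 | +16.7 | cheaper, worse | cheaper, better |

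**3. What follows for the displays, if they use the same definition.**

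- *Plane:* every point is reflected left to right, as in the last column.
- *Acceptability curve:* net benefit becomes λ(−ΔE) − ΔC. As the willingness to pay λ grows, the curve tends to the probability that confidence falls, not that it rises.
- *Interval:* limits (L, U) become (−U, −L).

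**4. What does not move.** The PAID ICER already has benefit as its denominator. The cost-utility ratio is per QALY. The Analyses section estimates differences between groups with 95% confidence intervals and attaches no direction to them.

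**The case against.** The best case on the other side is that this is a drafting slip. The intended direction is clear from several places in the article, no text argues that falling confidence is good, and a careful health economist would notice. Cost-effectiveness is a secondary outcome, and a wrong sign can be reversed without new data. All of that stands, and it limits the weight of the point. It does not remove it: the article states a formula, the formula conflicts with the hypothesis, and leaving it means that the sign is settled at analysis and not by the plan.

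Second, the scoring direction is inferred. The scale has been adapted for type 2 diabetes and transformed to 0–100, and its scoring source is not at hand. If it were reverse-scored, the wording would be consistent. That caveat stands, but nothing in the article suggests reverse scoring.

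Third, the ICER phrase might be parsed so that *reduction* governs only the PAID. The separate mention of a CIDS decrease in Sample size makes this unlikely.

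A reader might also infer more than the text supports:

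- *That the trial's conclusion on self-efficacy would be reversed.* It would not; the primary comparison does not use the ICER.
- *That the planes and curves will certainly be mirrored.* Economic analyses says only that they will be presented and does not define their effect axis.
- *That a negative CIDS ICER would by itself show the intervention to be dominated.* It would not, as the table shows: the same sign occurs in two opposite quadrants.

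**Conclusion.** The contradiction is real, and the ICER rule is wrong as written for the CIDS. Its size is a complete sign reversal of that one ratio, and it carries over to the CIDS plane, acceptability curve and interval only if they inherit the same effect definition. This rests on one assumption that the article does not state: that a higher CIDS score means more confidence.

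The reach is narrow. It covers the secondary economic analysis of one of the two primary scales and nothing else. The direction word in Sample size is a matter of consistency only. The point merits correction before the economic analysis is programmed, but it gives no reason to doubt the design or the primary analysis.

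**What to change.** - **Economic analyses:** define the denominator as the incremental mean reduction for the PAID and the incremental mean increase for the CIDS. Add that effects are coded so that positive is benefit in all planes and acceptability curves.
- **Sample size:** replace the CIDS decrease of 6 points with an increase, or with a difference to match the PAID sentence.
- **Measurements:** state which direction of the 0–100 CIDS score means greater confidence. If the adapted scale is in fact reverse-scored, say so; the present direction words would then be consistent and only that statement would be needed.

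The cost is a few words in three places, with no change to sample size, data collection or primary analysis.
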